**Methods::**

This study will be a single-center, randomized, double-blind, and placebo-controlled trial. Three groups, JCE 1000 mg, 2000 mg, and placebo, will be randomly allocated. Total duration of the clinical trial will be 12 to 14 weeks. Study participants will be followed up every 6 weeks and the effect and safety will be assessed at the 2^nd^, 3^rd^, and 4^th^ visit. All participants were asked to maintain a dosage schedule for this protocol. The primary outcomes will be measured using Korean Western Ontario and McMaster Universities Questionnaire and the secondary outcomes will include pain Visual analog scale score, EuroQol Five Dimensions questionnaire, Patient Global Impression of Change, and the changes in the laboratory test parameters of inflammation. Repeated-measure analysis will be used to measure primary efficacy based on full analysis set.

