### Study design

2.1

This study has been designed as a double-blind, single-center, randomized clinical trial for investigating the efficacy of JCE in KOA. A total of 36 subjects with KOA will be recruited from outpatients at the Daejeon University Cheonan Korean Medicine Hospital through advertisements posted on bulletin boards at hospitals, apartments, and so on. Recruitment commenced in April 2019, and the trial is expected to end in October 2019. All participants will receive a full written explanation of the study's protocol and an informed consent form. x-ray imaging of both knees will be performed for those who are suspected to have KOA based on history or physical examination. Additionally, blood tests for blood clotting factors, liver function, inflammation-related enzymes, and complete blood count will be performed. A total of 36 patients with knee pain who meet the eligibility criteria for this study will be randomly assigned in a 1:1:1 ratio to the treatment group 1 (JCE 1000 mg), treatment group 2 (JCE 2000 mg), or control group (placebo). The intervention will begin within 2 weeks of the screening visit. Based on the study group, the subjects will be administered JCE 1000 mg, JCE 2000 mg, or placebo for 12 weeks. The total duration of the clinical trial will be 12 to 14 weeks. Subjects will be followed up every 6 weeks, and the efficacy and the safety will be assessed at the 3^rd^ and 4^th^ visits. The study flow chart is presented in Figure 1.

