### Sample size calculation

2.3

We have demonstrated both in vitro and in vivo experiments that JCE has improved KOA and has antioxidant effects. To determine the minimum effective concentration, JCE was administered at various concentrations, and 100 mg/kg and 200 mg/kg of JCE was administered to the mice for 14 days, based on which it was confirmed that JCE had an excellent effect on improving the joint symptoms. Based on the US FDA guidelines for calculating the effective dose according to the body surface area in humans, the effective dose in the animal tests was calculated as the effective dose in terms of human body. Based on these calculations, the dose in the human body was set at 1000 mg and 2000 mg. Julius suggests that for the preliminary study and parallel design, the empirically optimal sample size is 12 persons per group, considering feasibility, estimated average, and dispersion accuracy.^[5]^ Therefore, we designed a pilot study with 12 subjects for each group.

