### Outcome measures

2.6

The primary outcome is Korean Western Ontario and McMaster Universities Questionnaire (K-WOMAC) score, which will be used to assess items related to knee pain, joint stiffness, and physical functioning in the 6^th^ and 12^th^ week of treatment. The secondary outcomes are pain visual analog scale score after 6 and 12 weeks of treatment, EuroQol Five Dimensions questionnaire survey score for rating quality of life, Patient's Global Impression of Change on treatment and the change of erythrocyte sedimentation rate, and C-reactive protein level, which indicated inflammation in the body. For safety of the subjects, we will conduct laboratory tests such as blood clotting factors, liver function, inflammation-related enzymes, and complete blood count, and evaluate vital signs. Safety assessments will be conducted at every visit. Participants’ data will be anonymized and coded by a specific program.

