### Statistical analysis

2.8

Statistical analysis will be primarily based on the principle of full analysis set. The missing values will be analyzed by the last observation carried forward method. For each of the 2 experimental groups and the control group, the baseline values before treatment and the changes in K-WOMAC at 6 and 12 weeks after treatment will be measured, and the descriptive statistics will include measurement of mean, standard deviation, median, minimum, and maximum. The analysis method for evaluation of the variables of efficacy involves confirmation of the normality of the values and then comparison using analysis of variance or Kruskal–Wallis test and post-test using Bonferroni method. The significance level will be set at *P* < .05 and the confidence interval at 95%. All statistical analyses will be performed using SPSS Statistics for Windows Version 20.0 (IBM Corp., Armonk, NY).

If necessary, subgroup analyses of outcome variables such as demographic variables measured at baseline (eg, sex, age, duration of illness, treatment expectation, and so on) can be performed. Safety assessments will be performed primarily by analyzing the frequency of adverse events and severe adverse events (SAEs) that researchers suspect to be related to treatment. The collected safety data will be summarized appropriately. All adverse events that occur will be listed with a detailed description. All SAEs will be recorded descriptively. The adverse events will be collected through patient symptom reporting and researcher observation. The frequency of each adverse event associated with or unrelated to the intervention will be recorded and analyzed using descriptive statistics. There is no intermediate analysis of this study, and the final decision regarding the completion of the clinical trial will be with the principal investigator.

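### The Abstract and section 2.8 name different primary efficacy analyses, and neither week 6 nor week 12 is made decisive

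*Protocol article*

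**What the plan says.** Two current statements in the protocol article describe the efficacy analysis.

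- **Abstract, Methods:** "Repeated-measure analysis will be used to measure primary efficacy based on full analysis set".
- **Section 2.8, Statistical analysis:** "confirmation of the normality of the values and then comparison using analysis of variance or Kruskal–Wallis test and post-test using Bonferroni method". This covers the efficacy variables in general. No separate method is given for the primary one, and repeated measures are not mentioned.

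Section 2.6 sets the primary outcome as K-WOMAC, covering pain, stiffness and "physical functioning in the 6^th^ and 12^th^ week of treatment". Section 2.8 adds that "the baseline values before treatment and the changes in K-WOMAC at 6 and 12 weeks after treatment will be measured". Neither section says which visit decides.

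Section 2.8 also states "The significance level will be set at *P* < .05" and "The missing values will be analyzed by the last observation carried forward method". Section 2.3 sets the size: "Therefore, we designed a pilot study with 12 subjects for each group".

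**The concern.** The two statements cannot both be the primary analysis, because they test different things. A repeated-measures analysis tests either the group effect averaged over visits or the group-by-time interaction. One-way ANOVA tests whether group means are equal at one visit, and Kruskal–Wallis compares ranks at one visit. No sentence gives one statement precedence, and with two follow-up visits the single-visit route is itself open.

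What is at stake is which hypothesis is tested, which effect is reported, and whether the result is called significant. An analyst could follow either statement and be faithful to the published text, including after the data are known.

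**Working it through.** **Inputs from the document.** Three arms allocated 1:1:1, 12 per arm, K-WOMAC at baseline, week 6 and week 12, significance level 0.05. The stated total reproduces: 3 × 12 = 36. There is no power calculation to reproduce.

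**Assumptions not in the document.** SD 1 at each visit; equal correlation ρ = 0.5 or 0.7 between visits; no missing data; 4,000 simulated trials per scenario. Effects in SD units, lower dose / higher dose:
- rising: 0.2 / 0.4 at week 6 and 0.4 / 0.8 at week 12;
- steady: 0.4 / 0.8 at both visits.

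**Procedures applied to the same data.** Change at visit t is c_t = y_t − y_0.
- S (section 2.8 at week 12): Shapiro–Wilk at 0.05 in each arm on c_12. If all three arms pass, one-way ANOVA; otherwise Kruskal–Wallis.
- R1 (Abstract): group-by-time F test over three visits, with 4 and 3 × 11 × 2 = 66 degrees of freedom.
- R2 (Abstract): group effect on (c_6 + c_12)/2, with 2 and 33 degrees of freedom.

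**Why they differ.** Take the higher dose against placebo with ρ = 0.5.
- Var(c_12) = 2(1 − ρ) = 1, so SD = 1.
- Var of the averaged change = (1 + ρ)/2 + 1 − 2ρ = 0.75, so SD = 0.866.
- Rising effect: 0.8/1 = 0.80 at week 12, against 0.6/0.866 = 0.69 for the average.
- Steady effect: 0.80 at week 12, against 0.8/0.866 = 0.92 for the average.

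Which method is favoured therefore depends on how the effect develops over time.

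**Results, normal data (% of trials)**

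| Scenario | S sig. | R1 sig. | R2 sig. | S, R1 disagree | S, R2 disagree |
|---|---|---|---|---|---|
| No effect, ρ 0.5 | 5.3 | 5.0 | 4.8 | 6.0 | 5.2 |
| No effect, ρ 0.7 | 5.2 | 5.5 | 4.9 | 6.4 | 5.4 |
| Rising, ρ 0.5 | 38.6 | 30.5 | 31.2 | 15.8 | 18.1 |
| Rising, ρ 0.7 | 56.7 | 46.8 | 44.9 | 16.7 | 20.6 |
| Steady, ρ 0.5 | 37.4 | 37.3 | 47.6 | 17.1 | 19.5 |
| Steady, ρ 0.7 | 55.7 | 60.5 | 69.5 | 18.6 | 20.5 |

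The simulation error on a 20% rate is about √(0.2 × 0.8/4000) = 0.6 percentage points.

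**Sensitivity to the assumptions.**
- Correlation 0.5 between baseline and follow-up and 0.7 between follow-ups, with a later effect (0.2 / 0.3 at week 6, 0.6 / 0.9 at week 12): week-12 ANOVA is significant in 47% of trials and R2 in 27%, and they disagree in 22%. A steady effect under these correlations gives 15% disagreement, and no effect about 4%.
- Skewed (log-normal) errors with an effect: S disagrees with R1 or R2 in about 21–34% of trials.

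**Undecided visit.** If section 2.8 were applied at weeks 6 and 12 and either counted, the false-positive rate would be 8.8–10.0% in simulation. Two independent tests would give 1 − 0.95² = 9.75%.

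**Normality check on its own.** With no effect, S rejects in 4.8–5.7% of trials across normal and skewed data. On normal data, three Shapiro–Wilk tests divert 12.6–14.9% of trials to Kruskal–Wallis (theory 1 − 0.95³ = 14.3%). The resulting decision differs from plain ANOVA in only 0.4% of trials with no effect and 1.4% with one.

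**The case against.** **The two statements may be one plan, condensed.** An abstract is a summary, section 2.8 is the operative text, and analysis of variance on changes at two visits could include the repeated-measures kind. This does not hold. Section 2.8 never says so, and the alternative it offers, Kruskal–Wallis, is an independent-groups test on one value per patient. Its natural partner is one-way ANOVA.

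**A separate analysis plan may settle it.** Covariance structure, degrees of freedom and the choice of normality test can properly be left there, and their absence is not criticised here. Two conflicting primary methods are different: an analysis plan would have to overrule one of them.

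**It is a pilot.** This stands in part. With 12 per arm chosen by a rule of thumb, no P value will be confirmatory, and section 3 acknowledges the small sample. But the article still names a primary efficacy analysis and a significance level, and section 3 says the study is meant to inform dose and duration.

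**Stronger readings that the documents do not support.** A reader might infer that the two methods could show effects in opposite directions. The check shows only significant versus not significant. A reader might also infer that choosing the test by a normality check breaks the 5% level. Under the assumptions tried, it does not do so materially.

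**Conclusion.** The contradiction is certain, since it rests on two current sentences. Its numerical size is conditional. With normal data, the two routes disagree on significance in about 15–22% of trials with an effect and about 4–6% with none; skewed data with an effect raise this to about 21–34%. These rates depend on assumed SD, correlations, effect patterns and complete data. Each method alone holds close to 5% (4.2–5.7%). The harm therefore comes from leaving the method and the visit open, not from any one test. The primary analysis should be settled before unblinding, while recognising that results from this pilot will be exploratory either way.

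**What to change.** State one primary analysis, in the same terms, in the Abstract and section 2.8. One workable version:

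- **Model:** mixed model for repeated measures on change in K-WOMAC total at weeks 6 and 12, with arm, visit, arm-by-visit and baseline K-WOMAC. Add the stratification factors actually used; section 2.4 says the randomisation is stratified but names none. Confirm that the total score is the one meant, since section 2.6 refers only to the K-WOMAC score.
- **Decisive comparisons:** each dose versus placebo at week 12.
- **Multiplicity:** keep Bonferroni for these two contrasts, 0.05/2 = 0.025 each. Unadjusted, two such contrasts gave at least one false positive in 9.2% of simulated null trials.
- **Missing data:** say that the model uses the observed data, with last observation carried forward as a labelled sensitivity analysis.
- **Rank-based test:** keep Kruskal–Wallis as a labelled sensitivity analysis, not as a branch that replaces the primary test.

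Naming a single-visit week-12 analysis in both places would also remove the contradiction.

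**Cost:** wording only, with no extra patients or data. Per-contrast thresholds are stricter than 0.05. If scores are clearly skewed, a normal-theory primary analysis can lose power: in the skewed rising scenario at ρ = 0.5, week-12 ANOVA was significant in 41.1% of trials and Kruskal–Wallis in 61.4%. That is a reason to report the rank-based result alongside.

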### Withdrawal and dropout

2.9

If the subject does not meet the inclusion or exclusion criteria or withdraws his/her consent, or if the subject's continued participation is judged as inappropriate, the subject will be excluded from the study. The researchers will record the reason for any interruption in the intervention and whether each participant completed the study.

### Safety

2.10

The occurrence of all adverse events will be assessed at each visit. Subjects will be monitored for undesirable, unintended symptoms, signs, and illnesses. The number and percentage of subjects who experience at least 1 adverse event will be calculated.

### Ethics

2.11

This study is designed based on the Helsinki Declaration and the Korean Clinical Practice Guidelines and has been approved by the Korean Institutional Review Board of DUCKMH (number DJUMC-2018-BM-09-3). This study protocol is registered with the Korean National Clinical Research Information Service (CRIS) (CRIS-KCT0003552). Subjects may be required to quit the study in case of serious adverse events or adverse drug reaction, and then they will be reported to institutional review board in a hospital. All participants of this study will be allowed to withdraw their consent at any time for any reason or discontinue their participation on a voluntary basis.

## Discussion

3

KOA is a chronic degenerative disease in which the articular cartilage is worn or damaged and clinically manifests as joint dysfunction owing to pain, stiffness, deformation, and edema of the joint tissue.^[6]^ Although the exact cause has not been elucidated yet, it is considered to be a major risk factor in wear of the joint because of aging and degeneration of the cartilage.^[7]^

Recently, KOA treatment has been aimed at relieving symptoms by reducing pain and edema. NSAIDs are frequently used as medications to reduce the inflammatory response.^[8]^ Treatments include drug therapy, physical therapy, surgery, and injection therapy.^[9]^ As KOA is a chronic disease, most people take NSAIDs for a long time, which often causes gastrointestinal side effects and nephrotoxicity.^[10]^ For these reasons, there is a growing interest in herbal medicines that are effective and safe in KOA.

*Juglandis semen* has been reported in various studies for its antioxidant and analgesic effects.^[11]^ Additionally, *Eucommia ulmoides* shows antioxidant activity and has anti-inflammatory effect.^[12,13]^*Acanthopanax sessiliflorum* is known to be effective for neuralgia, joint pain, and bruises.^[14]^ Further, *Zingiber officinale* is known to have anti-inflammatory and antioxidant effects.^[15]^ The purpose of this study is to investigate the efficacy of the combination of 4 herb medicines in KOA.

This is the first study at this stage to be conducted to determine the appropriate dosage and duration of JCE administration. However, the sample size may be small, and thus, a bias may occur. However, this study may provide insights into the mechanisms underlying the therapeutic effects of JCE in KOA and can lay the foundation for further studies on the effect of JCE on symptoms in patients with KOA.
